#### Interim outcomes

The interim outcomes (See Additional file 2) are listed below.The number of and type of publicly-available statements from food companies expressing support/non-support for healthier processed foods.The number of food companies with a nutrition policy published on their website.The level of engagement with the non-governmental organisation.The number of companies supporting the use of salt replacers/technologies in food processing to reduce the quantity of sodium required in processing.The number of companies supporting national salt reduction initiatives.The number of companies providing evidence of planned salt reduction.

#### Exploratory outcomes

Exploratory outcomes will be changes in average saturated fat (g/100 g), sugars (g/100 g), and energy density (kJ/100 g).

#### Sample size

The sample size for the study is 45 food companies and this will provide 80 % power to detect a difference of 50 mg/100 g in mean sodium content between the groups assuming the mean sodium content of products is 430 mg/100 g, the standard deviation for the sodium concentration is 300 mg/100 g and the intra-cluster correlation between products produced by the same company is 0.05 using a two-sided *T*-test with a significance level of 0.05. This would constitute an approximate 12 % reduction in sodium content of the foods produced by the intervention companies compared to the foods produced by the control group companies.

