**Methods/Design:**

This is a cluster-randomised controlled trial that will be done in Australia from 2013 to 2015 which includes 45 food companies. The 23 companies in the control group will receive no specific intervention whilst the 22 companies in the intervention group will receive an advocacy program based upon an established theory of change model. The primary outcome will be the mean change in sodium content (mg/100 g) of processed foods produced or marketed by intervention compared to control companies assessed at 24 months. Interim outcomes (statements of support, published nutrition policies, level of engagement, knowledge and use of technology to reduce salt, salt reduction plans, and support for national initiatives) will also be assessed and a qualitative evaluation will provide more detailed insight.

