^b^ Includes baby food, meal replacements, fitness and diet products, breakfast beverages, and sport protein powders

Australian Bureau of Statistics (ABS) definitions [39] were used to categorise companies as large (200+ employees), medium (20–199 employees) or small (0–19). Company ownership was determined using publicly available information and defined as being public or private [40]. The Australian New Zealand Standard Industrial Classification 2006 (ANZSIC) [41] was used to place companies into one or more food processing industry sectors. ANZSIC codes are used for the collection and reporting of financial, administrative and statistical data by government as well as by academics and the private sector [42]. The major food product categories in The George Institute Branded Food Composition Database were mapped against the ANZSIC system to identify the appropriate ANZSIC codes for each company. We identified 16 ANZSIC codes covering the relevant food manufacturing, grocery retailing and distribution (wholesaler) sectors (Table 2).

**Table 2 Tab2:** Baseline characteristics of intervention and control groups showing industry sector presence and company characteristics

Baseline characteristics of companies	Number	Intervention	Control
		n (%)	n (%)
Food companies:	45	22	23
Participation in industry sector^a^			
Cereal, Pasta and Baking Mix Manufacturing	17	9 (41)	8 (35)
Other Food Product Manufacturing n.e.c	24	14 (64)	10 (43)
Seafood Processing	11	7 (32)	4 (17)
Fruit and Vegetable Processing	25	13 (59)	12 (52)
Meat and Meat Product Manufacturing	1	1 (5)	0 (0)
Cured Meat and Smallgoods Manufacturing	7	3 (14)	4 (17)
Ice Cream Manufacturing	6	2 (9)	4 (17)
Cheese and Other Dairy Manufacturing	13	6 (27)	7 (30)
Milk and Cream Processing	8	3 (14)	5 (22)
Oil and Fat Manufacturing	5	2 (9)	3 (13)
Biscuit Manufacturing (Factory-based)	11	6 (27)	5 (22)
Bread Manufacturing (Factory-based)	8	4 (18)	4 (17)
Confectionery Manufacturing	6	2 (9)	4 (17)
Cake and Pastry Manufacturing (Factory-based)	5	2 (9)	3 (13)
Potato, Corn and Other Crisp Manufacturing	6	3 (14)	3 (13)
Meat Processing	4	2 (9)	2 (9)
Company size			
Large (≥200 employees)	36	17 (77)	19 (83)
Small-medium (<200 employees)	9	5 (23)	4 (17)
Company ownership			
Private	19	8 (36)	11 (48)
Public	26	14 (64)	12 (52)
Commitment to salt reduction 2010–2012 (Australian Division of World Action on Salt and Health)	10	4 (18)	6 (26)

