### Randomisation

Company ownership, size, and industry sector [28, 44–46] may influence corporate motivation and capability to produce and market more healthful processed food products. Baseline data for eligible food companies were collected and companies classified into three strata based on company ownership, size of company and industry sector. 18 blocks were created with companies in each block randomised in a 1:1 ratio to intervention or control. Randomisation was performed in December 2012 by an independent statistician using a random number function in SAS (Version 9.3). Food companies were not made aware that they had been randomised to intervention or control as a part of this study. The only individuals aware of the randomised allocations were those directly associated with the research team implementing the intervention program.

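### The stated 80% power for 50 mg/100 g cannot be reached with 45 companies, SD 300 and ICC 0.05; on those inputs the maximum is about 69%

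*Protocol article*

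**What the plan says.** The Sample size section gives the whole calculation in one sentence. It opens with the number of clusters and the claimed power: "The sample size for the study is 45 food companies and this will provide 80" per cent. The target is a between-group difference of 50 mg/100 g, set against an assumed average of 430 mg/100 g. The SD of the sodium concentration is 300 mg/100 g, the test is a two-sided t-test at the 0.05 level, and "the intra-cluster correlation between products produced by the same company is 0.05". The section equates the target with a reduction of roughly 12%, which agrees with 50/430 = 11.6%.

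The allocation is in the abstract: "The 23 companies in the control group will receive no specific intervention whilst the 22 companies in the intervention group will receive an advocacy program". Table 2 gives the same split. The Randomisation section confirms that companies are the randomised units: "companies in each block randomised in a 1:1 ratio to intervention or control".

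The section gives no number of products per company, no correlation between baseline and follow-up, and no other source of variance reduction.

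**The concern.** When companies are randomised, the between-company part of the variance shrinks only with the number of companies. Measuring more products within each company does not reduce it. Twenty-two and 23 companies at an ICC of 0.05 looked too few for a difference of one sixth of an SD (50/300), and the claim could fail whatever the cluster size.

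This is the only power statement for the primary outcome. The Discussion and conclusion say that a finding of no improvement will be read as support for government or policy action. How much weight such a result can carry depends on the power the trial had. If readers take 80% at face value, they will treat a null result as stronger evidence against a 12% reduction than the stated inputs allow.

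**Working it through.** **Inputs.** From the Sample size section: difference 50 mg/100 g, SD 300 mg/100 g, ICC 0.05, two-sided t-test at 0.05. From the abstract and Table 2: 22 intervention and 23 control companies. Products per company (m) are not stated in the Sample size section, so m is varied from 20, the eligibility minimum in Table 1, to infinity.

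**Formulas.**
- Variance of a company mean = SD² × [ICC + (1 − ICC)/m]
- SE of the difference = √{variance × (1/22 + 1/23)}
- Power from the noncentral t with 22 + 23 − 2 = 43 df, with the normal approximation alongside

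**Attempt to reproduce 80%, in the most favourable case (m → ∞).**
- Between-company SD = 300 × √0.05 = 67.1
- 1/22 + 1/23 = 0.0889
- SE = √(0.05 × 300² × 0.0889) = √400 = 20.0
- Difference/SE = 50/20.0 = 2.50
- 80% power by the normal approximation needs 1.96 + 0.84 = 2.80
- Power = Φ(2.50 − 1.96) = 70.5% (normal), or 68.6% (t, 43 df)

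The stated figure is not reproduced, and no value of m can change that.

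**Finite numbers of products, equal company sizes.**

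| Products per company | SE (mg/100 g) | Power, normal | Power, t | Difference detectable at 80% (t) |
|---|---|---|---|---|
| 20 | 27.9 | 43% | 42% | 80 |
| 50 | 23.5 | 57% | 55% | 67 |
| 100 | 21.8 | 63% | 61% | 63 |
| 356 | 20.5 | 68% | 66% | 59 |
| Unlimited | 20.0 | 70.5% | 68.6% | 57 |

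The 356 row is an assumption: 80% of about 20,000 products divided by 45 companies. It applies a 2011 database share to a general annual count that includes excluded food groups, so it is probably too high. Unequal company sizes would lower every finite-m row.

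**Companies needed.** For 80% power at 50 mg/100 g with the t-test: 30 per arm with unlimited products and 35 per arm at 100 products per company (29 and 34 by the normal approximation). The trial has 22 and 23.

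**Readings that would give about 80%.** Each contradicts the text.
- *45 companies per arm:* t-test power is 78% at 30 products and 85% at 50. The text gives 45 in total.
- *One-sided 0.05 test, unlimited products:* 80.4% (normal) or 79.2% (t). The text says two-sided.
- *Smaller ICC:* about 0.038 or less with unlimited products (t). The text says 0.05.

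**What baseline adjustment would have to supply.** To reach 80% with the t-test, the variance of a company mean must fall to 0.76 of its stated value with unlimited products, or 0.64 at m = 100. Let r be the company-level correlation between baseline and follow-up means.
- ANCOVA (factor 1 − r²): r = √(1 − 0.76) = 0.49, or √(1 − 0.64) = 0.60
- Change scores (factor 2(1 − r)): r = 1 − 0.76/2 = 0.62, or 1 − 0.64/2 = 0.68

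**The case against.** The best defence is that the planned analysis differs from the one the Sample size section describes. The Data analysis section tests the difference in change from baseline, and the same companies' products are surveyed in both years. The SD of 300 is that of the concentration, so the stated inputs do not determine the power of the change analysis. A moderate correlation between years could bring it to 80%. Stratified randomisation might also help if the strata enter the model. The article condenses a fuller protocol, so a correlation may have been used and left out. The Discussion also admits that only fairly large effects can be detected.

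Part of this stands. The trial's true power is not shown to be 69%, and it could be higher. It could also be lower: with change scores and r below 0.5, the factor 2(1 − r) exceeds 1. The loss of power is therefore conditional on the stated assumptions.

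The defence does not rescue the sentence. It names the clusters, SD, ICC, effect, test and significance level, and those values cannot yield 80%. The one plainly absent input, cluster size, does not matter because the ceiling already assumes infinitely many products. If a correlation was assumed, the calculation cannot be understood without it. The Discussion's caveat corrects neither the 80% nor the 50 mg/100 g.

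**Conclusion.** The concern holds. Under the protocol's own assumptions, 45 companies split 22 and 23 give at most 68.6% power for 50 mg/100 g (70.5% by the normal approximation), at least about 10 percentage points below the stated 80%. On those inputs a true reduction of about 12% would be missed 31% of the time at best, and 39% of the time at 100 products per company, compared with the 20% implied. The difference detectable with 80% power is at least 57 mg/100 g (57/430 = 13%).

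The ceiling rests only on figures printed in the article and does not depend on the unstated cluster size. The finite-m figures assume equal company sizes. The result concerns the power statement as written; the power of a baseline-adjusted analysis depends on a correlation that the article does not give.

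**What to change.** Choose one of two corrections to the Sample size section.

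1. **Restate the figure on the present basis.** For example: under these assumptions, 45 companies (22 and 23) give at most 69% power for 50 mg/100 g, and the difference detectable with 80% power is at least 57 mg/100 g (13%). Replace these limits with values computed from the actual product counts per company, allowing for their inequality.
2. **Base the calculation on the planned analysis.** State whether it is ANCOVA or change scores, quote the company-level correlation between years estimated from the existing annual database, give the product counts, and report the resulting power. Reaching 80% needs a correlation of about 0.49 to 0.60 for ANCOVA, or 0.62 to 0.68 for change scores, for unlimited and 100 products per company respectively.

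The cost is one recalculation and one rewritten sentence, with no extra companies and no change to the design or data collection. Under the first option the published figure becomes less favourable. Under the second it depends on the correlation found. Either way, the corrected figure should be in place before a null result is interpreted.

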### Data analysis

#### Primary outcome - quantitative

The primary null hypothesis to be tested is that there is no difference in the change in mean sodium content of foods from baseline to follow-up between intervention and control group companies. Comparable null hypotheses will be tested for each of the secondary and exploratory outcomes related to organisational actions and other measures of food composition. The characteristics of the companies and their food products will be summarised with continuous metrics reported as means with standard deviations (or medians with ranges if data are substantially skewed) and categorical characteristics as proportions.

The effects of the intervention on the primary outcome and other continuous variables will be determined using linear mixed models. Effects on categorical outcomes will be made using non-linear mixed models. All analyses will be done on the intention-to-treat basis with methods including adjustment for intra-cluster correlation. A p-value <0.05 will be deemed to indicate statistical significance. Primary analyses will be uni-variable but if there is evidence of imbalance in baseline characteristics between intervention and control companies’ adjusted models will be fitted to explore the likely impact of the imbalances. Quantitative statistical analyses will be done using Stata 13.1 (Stata Corp, College Station, TX, USA) and SAS (Version 9.3).

#### Interim outcomes

##### Quantitative

The number and proportion of food companies with the variable of interest will be calculated using Pearsons’s chi-squared test or Fisher’s exact test to assess for differences between control and intervention.

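### One chi-squared/Fisher rule covers all six interim outcomes but fits only the four that are yes/no per company; the statements count and the level of engagement need their own comparison

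*Protocol article*

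**What the plan says.** The protocol article lists six interim outcomes under Study outcomes, Interim outcomes. Four count companies that meet a condition, for example "The number of food companies with a nutrition policy published on their website". The other three of that kind are support for salt replacers or technologies, support for national salt reduction initiatives, and evidence of planned salt reduction.

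Two are of another kind:
- "The number of and type of publicly-available statements from food companies expressing support/non-support for healthier processed foods", a count with a direction;
- "The level of engagement with the non-governmental organisation", a graded quantity whose scale the article does not give.

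Under Data analysis, Interim outcomes, Quantitative, one sentence serves all six: "The number and proportion of food companies with the variable of interest will be calculated", with Pearson's "chi-squared test or Fisher’s exact test to assess for differences between control and intervention".

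The preceding section, Primary outcome - quantitative, has more general rules: "The effects of the intervention on the primary outcome and other continuous variables will be determined using linear mixed models", and "Effects on categorical outcomes will be made using non-linear mixed models".

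**The concern.** A proportion of companies answers the question of how many companies did something at all. The statements outcome asks how many statements were made and of which type. The analysis rule therefore does not estimate the quantity that the outcome definition names, and it leaves open whether supportive and non-supportive statements are scored separately. For engagement, neither named test uses the order of the levels, so a general shift upwards is not what is tested.

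At stake is part of the randomised evidence on the intermediate steps of the change model. With 45 companies that evidence is thin already, so discarding information matters more than it would in a large trial.

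**Working it through.** **No plan figure to reproduce.** The only power statement in the article (80%) concerns sodium content. None is made for an interim outcome.

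**Fit of rule to outcome.** Take four illustrative companies: A with 1 supportive statement, B with 10 supportive, C with 2 non-supportive, D with none.

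| Scoring | A | B | C | D |
|---|---|---|---|---|
| any statement | 1 | 1 | 1 | 0 |
| any supportive statement | 1 | 1 | 0 | 0 |
| supportive count | 1 | 10 | 0 | 0 |
| non-supportive count | 0 | 0 | 2 | 0 |

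Splitting by direction (second row) recovers the type. No yes/no scoring separates A from B in the way that the count does.

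**Power, statements.** From the documents: 22 intervention and 23 control companies; two-sided 0.05 (stated for the primary outcome). Assumed: Poisson or negative binomial counts per company, and a twofold rate ratio. The share of companies with any statement is 1 − exp(−μ) for Poisson and 1 − (1 + μ/k)^(−k) for negative binomial. For k=2 and μ=2 this is 1 − 2^(−2) = 75%; for μ=4 it is 1 − 3^(−2) = 89%. Simulated power, 3,000 runs per row (standard error at most √(0.25/3000) = 0.9 points):

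| Model, control v intervention mean | Any statement | Fisher, any/none | Pearson, any/none | Wilcoxon, counts |
|---|---|---|---|---|
| Poisson 0.25 v 0.5 | 22% v 39% | 20.3% | 24.4% | 24.2% |
| Poisson 0.5 v 1 | 39% v 63% | 30.1% | 33.3% | 43.1% |
| Poisson 1 v 2 | 63% v 86% | 36.3% | 44.2% | 73.7% |
| Poisson 2 v 4 | 86% v 98% | 13.2% | 27.3% | 96.5% |
| Neg. binomial k=2, 1 v 2 | 56% v 75% | 21.8% | 28.0% | 45.2% |
| Neg. binomial k=2, 2 v 4 | 75% v 89% | 16.5% | 24.0% | 59.2% |
| Neg. binomial k=1, 2 v 4 | 67% v 80% | 13.3% | 17.8% | 37.5% |
| Neg. binomial k=0.5, 1 v 2 | 42% v 55% | 10.6% | 12.0% | 18.5% |

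Separate simulations of the k=2, 2 v 4 case gave 15% to 16% for Fisher and 60% to 62% for the rank test. The loss is negligible when few companies speak at all and grows as most make at least one statement. With very uneven counts (k=0.5) both approaches are weak.

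**What a yes/no comparison can detect.** Power = Φ[(d − 1.96·s0)/s1], with s0 the pooled and s1 the unpooled standard error. For 20% v 60%: pooled proportion (23×0.2 + 22×0.6)/45 = 0.396; s0 = √[0.396×0.604×(1/23 + 1/22)] = 0.146; s1 = √(0.16/23 + 0.24/22) = 0.134; (0.4 − 1.96×0.146)/0.134 ≈ 0.85, so power is about 80%. From a control rate of 50%, the other arm must reach about 88%.

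**Power, engagement.** Assumed: four ordered levels.
- Controls spread evenly, common odds ratio 5: Wilcoxon 82%, Pearson on all four levels 66%, Fisher on a single cut 33% to 70% depending on the cut.
- A shift from 40/30/20/10% to 15/25/30/30%: rank test 66%, Pearson on all levels 48%, Fisher on any/none 41%.

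**The case against.** The strongest reply is that this is a condensed article. Its list opens with "The interim outcomes (See Additional file 2) are listed below", and that file, which is not shown, may define a company-level indicator for each outcome. The analysis sentence is generic, the outcome definition already distinguishes support from non-support, and the mixed-model rules in the preceding section could take up non-binary outcomes. The company is the randomised unit, and a proportion is not dominated by a few prolific communicators. A qualitative evaluation runs alongside.

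Much of this stands, and it limits what may be claimed. A reader might infer any of the following, but the documents do not support them:
- *Most of the power is lost.* No statement rates are given, and under plausible rates the loss runs from nil to almost total.
- *Opposing statements would count as success.* The rule does not say that the directions are pooled. It only fails to say that they are not.
- *Engagement is cut to any/none.* Pearson's test takes several levels, and nothing says that they are collapsed.
- *Statements are near ceiling because 36 of 45 companies are large and 22 of 45 had joined a Food and Health Dialogue target.* Neither figure is a statement rate. The same table shows only 10 of 45 with an earlier salt-reduction commitment and 7 of 45 in the industry council's healthy commitment.

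The mismatch itself remains. The article is not silent: it states a rule, and that rule cannot carry a count. Additional file 2 is cited as describing the outcomes, not for their analysis. The mixed-model rules are general, whereas the chi-squared/Fisher rule is specific to interim outcomes. If the general rules were meant to govern, the two sections would name different methods for the same outcomes and would need reconciling anyway.

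**Conclusion.** The point holds as a minor one. The stated rule fits four of the six interim outcomes. For the statements outcome it discards the number and leaves the handling of direction unstated. For engagement it ignores order, which costs a moderate amount of power (82% to 66%, or 66% to 48%, in the two cases above when all levels are kept).

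For statements, the cost of any/none scoring by Fisher against a rank test on counts runs from slight when statements are rare (about 20% v 25%) to large when most companies make at least one (about 15% v 60% at means of 2 v 4, k=2). These figures rest on assumed rates, dispersion and a doubling between arms; they illustrate the range and do not forecast the trial. The primary sodium outcome is not affected.

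**What to change.** In Data analysis, Interim outcomes, Quantitative:

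1. Limit the chi-squared/Fisher rule to the four outcomes that are yes/no per company.
2. For statements, derive two counts per company, supportive and non-supportive, and compare each between arms with a Wilcoxon rank-sum test or a negative binomial model, with the company as the unit. Name one of these as the main test in advance.
3. For engagement, compare the ordered levels with a Wilcoxon test or a proportional-odds model.
4. Keep the number and proportion of companies as descriptive figures for these two outcomes.

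The cost is wording. The article's section on intervention monitoring data says that the interim-outcome data will be recorded for both intervention and control companies, so no new collection is evident. The downside is that model-based effects appear as rate or odds ratios, which are less immediate than a difference in proportions; the descriptive proportions offset that.

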Participant of any Food and Health Dialogue salt reduction target 2009-2013	22	9 (41)	13 (57)
Use of Heart Foundation Tick logo on front-of-pack 2013	24	9 (41)	15 (65)
Member of Australian Food and Grocery Council Healthy Commitment 2013	7	3 (14)	4 (17)

^*a*^Australian and New Zealand Standard Industrial Classification (ANZSIC) [42]. One or more ANZSIC class descriptions can apply to a single food company

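### The interim company outcomes are given a two-group chi-squared or Fisher test with no place for baseline status, while the same article elsewhere specifies change hypotheses and mixed models

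*Protocol article*

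**What the plan says.** Under Data analysis, Interim outcomes, Quantitative, the article compares the number and proportion of companies with the variable of interest by Pearson's chi-squared or Fisher's "exact test to assess for differences between control and intervention". It mentions neither a time point nor a baseline term.

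The section just before it, headed Primary outcome - quantitative, states the primary null hypothesis as no difference in change from baseline. It then adds: "Comparable null hypotheses will be tested for each of the secondary and exploratory outcomes related to organisational actions". It also says: "Effects on categorical outcomes will be made using non-linear mixed models". The same section allows adjusted models if baseline characteristics prove imbalanced, in order to explore the likely impact.

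The interim outcomes include "The number of companies supporting national salt reduction initiatives". Table 2 has a baseline row of a similar kind, "Participant of any Food and Health Dialogue salt reduction target 2009-2013", with 9 of 22 intervention companies (41%) and 13 of 23 control companies (57%). Surveys of companies says that company data are collected at baseline, midway and completion, and that public-source information is compiled for all companies.

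**The concern.** The two sections differ in method (mixed model v 2x2 test) and in hypothesis (change v level). Among the listed outcomes, only the interim ones fit the description of organisational actions, so the general statement appears to reach them.

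The difference matters because many companies may already show the behaviour being counted. A two-group test of proportions scores a company that was already on board the same as one that joined during the programme. The interim outcomes are the logic model's quantitative evidence on whether the advocacy pathway operated. A null result from an insensitive test could be misread as failure of the theory of change.

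**Working it through.** **Inputs from the article.** There are 22 intervention and 23 control companies, and the significance level is 0.05. Baseline Dialogue participation is 9/22 and 13/23 (Table 2).

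**Assumptions, not in the article.** Dialogue participation stands in for supporting national salt initiatives. Baseline supporters all persist and are counted at follow-up. Non-supporters convert independently at rate i (intervention) or c (control).

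**1. Table 2 reproduced.** 9/22 = 40.9% and 13/23 = 56.5%, a gap of 15.6 points. Fisher p = 0.38 (chi-squared p = 0.29). The other three engagement rows also have control ahead:
- Heart Foundation Tick: 15/23 v 9/22 (65% v 41%), Fisher p = 0.14
- salt commitment: 6/23 v 4/22 (26% v 18%), p = 0.72
- Healthy Commitment membership: 4/23 v 3/22 (17% v 14%), p = 1.0

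Each is compatible with chance.

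**2. What the stated test would need.** If control stays at 13/23, 18/22 gives Fisher p = 0.11 and 19/22 gives p = 0.047. So 19 - 9 = 10 of the 13 intervention non-participants would have to join.

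**3. Expected follow-up proportions.** Intervention is (9 + 13i)/22 and control is (13 + 10c)/23.
- i = 50%, c = 10%: 15.5/22 = 70.5% v 14/23 = 60.9%, a difference of 9.6 points. The difference in change is 6.5/22 - 1/23 = 29.5 - 4.3 = 25.2 points.
- i = 30%, c = 10%: 12.9/22 = 58.6% v 60.9%. Control looks slightly better although intervention companies convert at three times the rate.
- i = c = 10%: 10.3/22 = 46.8% v 60.9%. With no effect, control looks 14 points better.

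**4. Chance of p < 0.05 in favour of the intervention.** This is the sum of Binomial(13, i) × Binomial(10, c) probabilities over all tables that Fisher's test rejects.

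| Conversion, intervention v control | Stated test, all 45 companies | Fisher among the 13 + 10 baseline non-supporters |
|---|---|---|
| 30% v 10% | <0.1% | 13% |
| 50% v 10% | 2.1% | 44% |
| 50% v 20% | 0.9% | 22% |
| 60% v 10% | 8.4% | 64% |

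Under the persistence assumption, an exact test stratified by baseline status gives the right-hand column, because a stratum in which every company is a supporter carries no information. A linear model of follow-up status on arm and baseline status, simulated 3,000 times, gave about 57% at 50% v 10%. The figure depends on the method, but the direction does not.

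**5. Separating the two causes.** The 50% v 10% case was repeated with near-equal starts:
- 11/22 v 12/23: stated test 8.7%, non-supporter comparison 36%
- 11/22 v 11/23: stated test 14.9%, non-supporter comparison 51%

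Removing control's head start raises the stated test from 2% only to 9-15%. The larger part of the shortfall is dilution by companies already on board.

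**The case against.** - **Follow-up-only is an inference.** The interim-outcome sentence names no time point and does not define its variable, and the fuller outcome descriptions are in Additional file 2, which is not shown. A chi-squared or Fisher test could be applied to newly adopted behaviour. This stands. What the text does show is a test without a baseline term, set against a hypothesis on change.
- **Adjustment is already offered.** If the general section governs the interim outcomes, its adjusted models do too. That is fair, but those models are conditional and exploratory, sit under the primary-outcome heading and are not carried into the interim section. If that section covers only the primary outcome, most of the conflict goes. Its reference to organisational actions makes that reading hard to hold.
- **The specific rule may override the general one.** The interim test has its own heading, and one yes/no per company at one time has no clustering to model. A reader might infer an open choice between two p-values. The text supports the narrower statement that the two passages need aligning.
- **The test is valid.** A reader might infer that it is biased against the intervention. Allocation was random, the imbalance is compatible with chance, and type I error is kept. The tilt exists only conditional on this baseline.
- **The illustration is narrow.** Dialogue participation is a proxy for one of six outcomes, no baseline figures are shown for the other five, and the conversion and persistence rates are assumed. All of this stands.
- **Baseline values may be missing.** Companies were invited to the baseline survey, non-participation is an acknowledged risk, and salt-replacer items come from a short questionnaire within an advocacy action. This limits where the fix can apply.

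**Conclusion.** The point holds in a limited form. The two analysis sections disagree on method and hypothesis for the interim company outcomes, and the test named for them cannot use baseline status that the trial plans to collect.

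The cost is lost power and, for this baseline, an estimate leaning towards control. It is not a false-positive problem. In the illustration at 50% v 10% conversion, rejection is about 2% with the stated test (9-15% with near-equal starts) against about 44% among baseline non-supporters. This rests on full persistence of baseline supporters, assumed conversion rates and a proxy outcome.

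A reader might conclude that control's 57% v 41% lead is the main cause, but the near-equal-start calculation does not support that. The primary sodium comparison is untouched and the interim outcomes are read alongside a qualitative evaluation, so the severity is minor to moderate.

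**What to change.** Reconcile the two sections so that one method and one hypothesis apply to the interim outcomes. For each yes/no interim outcome with a baseline value from the survey or public sources, use one company-level analysis at follow-up, adjusted for the company's own baseline status. Use penalised or exact logistic regression where cells are sparse; ordinary logistic regression fails if all baseline adopters persist. Add a table of conversions among baseline non-adopters by arm. Keep Fisher's test where no baseline value exists, and say which outcomes those are.

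The cost is a change of wording and a little more analysis. No new data collection is needed for outcomes whose baseline status comes from public sources or completed baseline surveys.
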